### Protocol summary

#### Study aim

To determine the short term effects of strengthening exercises of lower limb rehabilitation protocol on pain, stiffness, physical function and body mass index among knee osteoarthritis participants who are overweight or obese

#### Design

The study will be single blinded randomized controlled design. Three research coordinators will be involved in data collection. The one coordinator will be involved in baseline data collection and two coordinators will be involved in the assessment of outcomes. Participants will be blinded of other groups intervention.

#### Settings and conduct

The study will be conducted at the urban area of Lahore Pakistan and measurements will be assessed at the Teaching Bay of Rehmatul-Lil-Alameen Postgraduate Institute

#### Participants/Inclusion and exclusion criteria

Inclusion Criteria: Overweight or obese knee osteoarthritis participants, age between 45 and 60 years, residing in the urban community of Lahore, second and third degree of knee changes according to Kellgren and Lawrence radio-graphic scale Exclusion Criteria: System lupus erythematosus, Flat feet, Spinal deformities, Participants having history of metabolic, hormonal, orthopaedic and cardiovascular diseases, Previous surgery of knee/s of any cause The patients who had any injections of knee/s in the last six months or Unable to walk independently

#### Intervention groups

Intervention 1: Intervention group 1 the strengthening exercises of the lower limbs and instructions of daily care. The training session will be of 30-40 minutes. It will consist of three times a week for 4 weeks at their houses. Intervention 2: Intervention group 2 the

participants in this group will follow the instructions of daily care only as a usual care for duration of 4 weeks at their houses.

#### Main outcome variables

Primary: Knee pain, stiffness and physical function  
Secondary: Patients, s satisfaction and exercise adherence

### General information

#### Reason for update

#### Acronym

#### IRCT registration information

IRCT registration number: **IRCT20191221045846N2**  
Registration date: **2020-06-28, 1399/04/08**  
Registration timing: **prospective**

Last update: **2020-06-28, 1399/04/08**

Update count: **0**

#### Registration date

2020-06-28, 1399/04/08

#### Recruitment status

**Recruitment complete**

#### Funding source

**Expected recruitment start date**

2020-07-10, 1399/04/20

**Expected recruitment end date**

2020-08-09, 1399/05/19

**Actual recruitment start date**

empty

**Actual recruitment end date**

empty

**Trial completion date**

empty

**Scientific title**

Short term effects of strengthening exercises of lower limb rehabilitation protocol (LLRP) on pain, stiffness, physical function and body mass index (BMI) among knee osteoarthritis (OA) participants who are overweight or obese.

**Public title**

Short term effects of exercises among knee osteoarthritis (OA) participants who are overweight or obese.

**Purpose**

Treatment

**Inclusion/Exclusion criteria****Inclusion criteria:**

Overweight or obese knee OA participants aged between 45 to 60 years. Familiar with WhatsApp application Participants will be chosen from the urban area community of Punjab Lahore, Pakistan. The sample included males and females having OA of one or both knees confirmed by medical specialist according to the Kellgren and Lawrence radiographic scale for the assessment of OA

**Exclusion criteria:**

Rheumatoid arthritis System lupus erythematosus Flat feet Spinal deformities Unable to walk independently History of metabolic, hormonal, orthopaedic or cardiovascular disease Previous surgery of knee/s Injections of knee/s for the last six months.

**Age**

From **45 years** old to **60 years** old

**Gender**

Both

**Phase**

2

**Groups that have been masked**

- Participant
- Outcome assessor
- Data analyser
- Data and Safety Monitoring Board

**Sample size**

Target sample size: **50**

**Randomization (investigator's opinion)**

Randomized

**Randomization description**

The researcher will allocate the selected knee osteoarthritis participants into two groups, namely, Rehabilitation Protocol Group (RPG) and Control Group (CG) by simple random technique using a computer-generated random number. The participants in the RPG will follow the strengthening exercise of LLRP and IDC for

duration of 4-weeks. The participants in the CG will not involved in the rehabilitation protocols, but these participants will follow only the IDC for the duration of 4-weeks at their houses.

**Blinding (investigator's opinion)**

Single blinded

**Blinding description**

The principle investigator will not be blinded. The participants receiving the intervention will be blinded by simply not informing them of their treatment allocation. The coordinators collecting data will be independent individuals from trials and will be unaware of the group allocation. There will be different coordinators at the initial and final evaluation. Individuals performing the statistical analysis will be blinded by labelling the groups with non-identifying terms (such as X and Y).

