## **Intervention groups**

## **1**

### **Description**

The participants in this group (Rehabilitation Protocol Group) will perform the strengthening exercises of lower limb rehabilitation protocol (LLRP) and follow the

instructions of daily care (IDC) for duration of four weeks at their houses according to the provided leaflet. Each training session of strengthening exercises will be performed three times a week for four weeks at their houses. These training sessions were the strengthening exercises of lower limbs in non-weight bearing sitting and lying positions. Each training session will consist of 45–60 minutes of training followed by 10 minutes warm up at the start and 10 minutes cool down at the end of training protocol.

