## **2**

### **Description**

The participants in this group (Control Group) will follow only the instructions of daily care (IDC) for duration of four weeks at their houses according to the provided leaflet.

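### Participants are declared masked although they know whether they are exercising, so the three self-reported primary outcomes are effectively unblinded, and the single-blind label conflicts with the list of masked parties

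*Protocol*

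**What the plan says.** The protocol describes masking in four places.

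- **Groups that have been masked** names four parties: participant, outcome assessor, data analyser, and Data and Safety Monitoring Board.
- **Blinding description** gives the mechanism for participants: "The participants receiving the intervention will be blinded by simply not informing them of their treatment allocation". For data collection it says: "The coordinators collecting data will be independent individuals from trials and will be unaware of the group allocation". It adds that different coordinators act at the first and last evaluation, that the analysts see neutral group labels such as X and Y, and that the principal investigator is not blinded.
- **Blinding (investigator's opinion)** reads "Single blinded", and the Design paragraph of the Protocol summary uses the same term.
- That **Design** paragraph describes participant blinding more narrowly: "Participants will be blinded of other groups intervention".

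On treatment, the first entry under Intervention groups says of the exercise arm: "Each training session of strengthening exercises will be performed three times a week for four weeks at their houses". That arm also receives the daily-care instructions. The second entry says the control arm "will follow only the instructions of daily care (IDC) for duration of four weeks at their houses according to the provided leaflet". The Placebo field says that none is used, and no sham exercise is described. Each of the three primary outcomes (knee pain, stiffness, physical function) is measured by the WOMAC score at baseline and after four weeks.

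**The concern.** A participant is masked if he or she cannot tell which treatment is being received. Someone who has been given a strengthening programme and carries it out at home for four weeks can tell, and so can someone who has been given care instructions and no exercises. Leaving the allocation unspoken changes neither.

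The error matters because of where it falls. All three primary outcomes are ratings of the participant's own pain, stiffness and function. If the protocol stands as written, a report could call these results participant-blind and assessor-blind, and a reader would give them more weight against expectation effects than the design can support. The conflicting descriptions also leave it open which parties the single-blind label is meant to cover.

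**Working it through.** The protocol gives no figure on this point, so the main check is to compare its sections.

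**1. Can participants be masked by the stated mechanism?**

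| Section | Content | Consequence |
|---|---|---|
| Groups that have been masked | Participant is listed | Property claimed |
| Blinding description | Participants are not told their allocation | Only mechanism offered |
| Randomization description; Intervention groups 1 and 2 | Strengthening sessions plus daily care, against daily care only | The arms differ in what the participant does |
| Placebo | None; no sham described | Nothing makes the arms look alike |
| Design (Protocol summary) | Participants do not learn what the other arm receives | Hides the alternative, not one's own treatment |

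The claimed property does not follow from the mechanism. The Design wording describes something that is feasible, but it is not masking of allocation.

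**2. Does the label agree with the list?** The label is single blind. The list has four parties, and the Blinding description itself covers three of them (participants, coordinators, analysts). No section says which one party the label refers to.

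**3. Which outcomes are affected?**

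| Outcome | Measurement stated | Rests on the participant's own rating? |
|---|---|---|
| Knee pain, stiffness, physical function (primary) | WOMAC | Yes, by inference; mode of administration is not stated |
| Satisfaction (secondary) | 0 to 10 rating | Yes |
| Exercise adherence (secondary) | 0 to 10 rating | Rater not stated |
| BMI (secondary) | Weight and height | No |

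A coordinator unaware of the group who records the answer of an unmasked participant does not make that answer blind.

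**4. What could a reporting shift do? (illustration)**

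Inputs:
- Total of 50 from the Sample size field.
- Assumed: 25 per arm, a two-sample t-test at two-sided 5%, and no true effect.
- Assumed: a shift of d standard deviations in self-report, caused by knowing one's treatment.

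The test statistic follows a noncentral t distribution with 25 + 25 − 2 = 48 degrees of freedom and noncentrality d × √(25/2) = 3.536 × d. The critical value is 2.011. The probability of a significant result is P(T > 2.011) + P(T < −2.011).

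| Shift d (SD) | Noncentrality | Chance of p < 0.05 (t) | Normal approximation |
|---|---|---|---|
| 0 | 0 | 5.0% | 5.0% |
| 0.2 | 0.707 | 10.7% | 10.9% |
| 0.3 | 1.061 | 18.0% | 18.6% |
| 0.4 | 1.414 | 28.3% | 29.3% |

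These are rates for one primary outcome taken alone. The two columns differ only through the normal approximation.

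**The case against.** The strongest reply is that an exercise programme can rarely be hidden from the people doing it, so an open design is no fault, and that the protocol has safeguards that do work. Both parts stand. Coordinators unaware of the group can limit prompting and uneven handling when WOMAC is collected, and they protect the BMI measurement. Analyst masking by neutral labels is unaffected. Because both arms work at home from a leaflet, not revealing the other arm's content may also soften expectation, although the public title names exercise as the subject of the study. None of this rescues the statement that participants are masked.

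Three stronger readings are tempting, and the protocol does not support them.

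- A reader might infer that no protection against bias exists at all. The Blinding description sets out coordinator and analyst masking, and nothing there makes either impossible. Coordinator masking does need care, because an adherence rating taken after four weeks could reveal the arm, and the protocol does not say who collects it or from whom.
- A reader might infer that the control arm has less contact with staff. The protocol describes no supervision and no difference in contact. The stated difference is exercise content.
- A reader might take 10.7% to 28.3% as the trial's actual error rate. The protocol contains no evidence on the size of any reporting shift, and its simple randomisation does not guarantee 25 per arm.

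It is also fair to say that the protocol does not state how WOMAC is administered. Self-report is an inference, but a sound one for a person's own pain, stiffness and function.

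**Conclusion.** The concern holds. Participant masking is declared but cannot be achieved by the stated means, and the single-blind label conflicts with the four-party list. The three primary outcomes are effectively unblinded, provided that WOMAC rests on participants' answers. Masking of coordinators and analyst remains possible and useful.

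The error lies in what the protocol claims, not in the choice to run an exercise trial without participant masking. It should still be corrected, because it misdescribes a main safeguard behind every primary outcome and so changes what can be concluded from them. The probabilities above show how sensitive a trial of this size would be to a modest shift. They depend on the assumed shift, the 25 per arm and the t-test, and the verdict does not depend on them.

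**What to change.** - In **Groups that have been masked**, delete the participant entry.
- In **Blinding description**, delete the sentence quoted first from that section and put in its place: *Participants are not masked to their own treatment; they are not told the content of the other arm. Data-collecting coordinators and the analyst (groups labelled X/Y) are unaware of allocation. WOMAC and satisfaction ratings rest on participants' own reports and are therefore not blinded.*
- In **Design** and **Blinding (investigator's opinion)**, replace the single-blind wording with: *coordinators (outcome assessors) and data analyst masked; participants not masked*. If the monitoring board stays in the list of masked parties, name it here too so that label and list agree.
- State conclusions on pain, stiffness and function as effects on unblinded participant-reported outcomes.

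The new text should not claim that the study hypothesis is concealed from participants, since no section says so. The cost is protocol and registry wording. The stated design will look less favourable, and no procedure changes.

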**Placebo**

Not used

**Assignment**

Parallel

**Other design features****Secondary Ids**

empty

**Ethics committees****1****Ethics committee****Name of ethics committee**

Ethical Committee RAIC PESSI (Rehmatul-Lil-Alameen Postgraduate Institute of Cardiology, Punjab Empl

**Approval date**

2020-05-20, 1399/02/31

**Ethics committee reference number**

RAIC PESSI/Estt/2020/36

**Health conditions studied****1****Description of health condition studied**

Osteoarthritis of knee

**ICD-10 code**

M17

**ICD-10 code description**

Osteoarthritis of knee

**Primary outcomes****1****Description**

knee pain

### **Timepoint**

at baseline and after 4 weeks of intervention

### **Method of measurement**

Western Ontario and McMaster Universities Osteoarthritis Index (WOMAC) score

## **2**

### **Description**

Stiffness

### **Timepoint**

At baseline and after 4 weeks of intervention

### **Method of measurement**

WOMAC score

## **3**

### **Description**

Physical function

### **Timepoint**

At baseline and after 4 weeks of intervention

### **Method of measurement**

WOMAC score

## **Secondary outcomes**

## **1**

### **Description**

Body Mass Index

### **Timepoint**

At baseline and after 4 weeks of intervention

### **Method of measurement**

Calculated by the formula Weight (kg)/Height(meter square)

## **2**

### **Description**

Patients satisfaction

### **Timepoint**

After 4 weeks of intervention

### **Method of measurement**

Numeric rating scale ranging from 0 to 10

## **3**

### **Description**

Exercise adherence

### **Timepoint**

After 4 weeks of intervention

### **Method of measurement**

Numeric rating scale ranging from 0 to 10

## **Intervention groups**

## **1**

### **Description**

The participants in this group (Rehabilitation Protocol Group) will perform the strengthening exercises of lower limb rehabilitation protocol (LLRP) and follow the

instructions of daily care (IDC) for duration of four weeks at their houses according to the provided leaflet. Each training session of strengthening exercises will be performed three times a week for four weeks at their houses. These training sessions were the strengthening exercises of lower limbs in non-weight bearing sitting and lying positions. Each training session will consist of 45–60 minutes of training followed by 10 minutes warm up at the start and 10 minutes cool down at the end of training protocol.

### **Category**

Treatment - Other

## **2**

### **Description**

The participants in this group (Control Group) will follow only the instructions of daily care (IDC) for duration of four weeks at their houses according to the provided leaflet.

### **Category**

Treatment - Other

## **Sponsors / Funding sources**

## **1**

### **Sponsor**

#### **Name of organization / entity**

Rehmatul-Lil-Alameene Post Graduate Institute of Cardiology

**Grant name**  
**Grant code / Reference number**  
**Is the source of funding the same sponsor organization/entity?**  
Yes  
**Title of funding source**  
Rehmatul-Lil-Alameene Post Graduate Institute of Cardiology  
**Proportion provided by this source**  
50  
**Public or private sector**  
Public  
**Domestic or foreign origin**  
Domestic  
**Category of foreign source of funding**  
empty  
**Country of origin**  
**Type of organization providing the funding**  
Other

## 2

**Sponsor**  
**Name of organization / entity**  
University of Malaya  

**Grant name**  
**Grant code / Reference number**  
**Is the source of funding the same sponsor organization/entity?**  
No  
**Title of funding source**  
N/A  
**Proportion provided by this source**  
50  
**Public or private sector**  
Public  
**Domestic or foreign origin**  
Foreign  
**Category of foreign source of funding**  
Sponsor: country of origin

**Country of origin**  
PK  
**Type of organization providing the funding**  
Other

## Sharing plan

**Deidentified Individual Participant Data Set (IPD)**

Undecided - It is not yet known if there will be a plan to make this available

**Study Protocol**

Undecided - It is not yet known if there will be a plan to make this available

**Statistical Analysis Plan**

Undecided - It is not yet known if there will be a plan to make this available

**Informed Consent Form**

Undecided - It is not yet known if there will be a plan to make this available

**Clinical Study Report**

Undecided - It is not yet known if there will be a plan to make this available

**Analytic Code**

Undecided - It is not yet known if there will be a plan to make this available

**Data Dictionary**

Undecided - It is not yet known if there will be a plan to make this available
